***Randomisation ***will use permuted block randomisation using computer generated quasi-random numbers. Randomisation will be stratified according to recruitment locality (4 sites, enabling a steady flow to treatment groups) and participants' symptomatic status at intake assessment (asymptomatic *vs*. partially symptomatic), using the GRID-Hamilton Rating Scale for Depression GRID-HAMD [31] cut-off of less than eight being asymptomatic and greater than or equal to 8 being partially symptomatic.

Figure 1 summarises the trial Consort diagram.

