### Sample size

Different relapse prevention interventions with different populations produce different absolute rates of depressive relapse/recurrence. Therefore, we have based our sample size on estimated hazard ratios for MBCT *vs*. m-ADM rather than estimated absolute relapse/recurrence rates. We canvassed service users and clinicians who concurred that a relative reduction in relapse/recurrence of 10% would be clinically important. ***(i) The policy question: ***The systematic review of MBCT *vs*. usual care for patients with recurrent depression reports hazard ratios of .47 and .28 for the key trials [24]. We applied several conservative assumptions (first row of Table 1). First, even though the exploratory trial data suggest that the hazard ratio was improving in favour of MBCT as the length of follow-up increased [25], we assumed the hazard ratio of .63 at 15 months to power the proposed trial at 24-months follow up. Second even though attrition from MBCT trials to date is consistently <15%, we have assumed an attrition rate of 20% over the 24-months of follow-up. Finally, we assumed there may be a small clustering effect (ICC = 0.01). The resultant sample size calculation assumptions and output are shown in Table 1 based on 80% power and significance set at .05. This leads to a total sample size of 420 across the two groups.

**Table 1 T1:** Sample size calculation

Author	Comparison	Mean hazard ratio	ICC	Design factor**	Attrition rate	**Sample size per group**^**a**^
Conservative scenario	MBCT *vs*. m-ADM	0.63	.01	1.11	20%	210

Kuyken et al., 2008 [25]	MBCT *vs*. m-ADM	0.63	-0.02	1.0	7%^a^	160

Ma & Teasdale, 2004 [22]	MBCT *vs*. usual care	0.28	-0.008	1.0	3%^b^	14^c^

Teasdale et al., 2000 [23]	MBCT *vs*. usual care	0.47	-0.04	1.0	5%^b^	41^c^

Sample size necessary for 90% power at 5% significance at 24 months;

^a ^at 15 months; ^b ^at 60 weeks, ^c^assuming exponential survival function.

Note group size of 12

***For the secondary outcomes***, meta-analyses of generic mindfulness approaches suggest medium effect sizes in changes in depressive symptoms [19,40] and our exploratory trial suggests medium effect sizes for the secondary outcomes of residual depressive symptoms, psychiatric co-morbidity and quality of life [25]. The sample size estimate for our policy question will enable us to detect a medium between-groups effect size (standardised mean difference or Cohen's d = 0.40) on the main secondary outcomes.

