#### Secondary outcomes

A unique aspect of our trial is the inclusion of a range of secondary outcome measures including those highly valued by patients themselves. Residual depressive symptoms will be assessed with the observer-rated interviewer administered 17-item HRSD [43] and a well established self-report measure, the [Beck Depression Inventory, 2nd edition; [44]]. Psychiatric co-morbidity will be assessed with the full SCID, and medical co-morbidities with a screening questionnaire. Depression free days will be calculated from the SCID. Quality of life will be assessed with the EQ-5D health-related quality of life measure [45,46].

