### Statistical analysis plan

Analyses will be conducted by the trial statistician (RT) following CONSORT standards and overseen by the Data Monitoring and Safety Committee. Initial analyses will be conducted on an intention to treat (ITT) basis, with subsequent analyses being per protocol. All statistical models will be run with and without adjustment for baseline characteristics where the covariate selection is derived from comparison of the treatment groups at baseline.

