#### (i) The policy question

For the primary outcome variable, time to relapse/recurrence will be compared using Cox regression proportional hazard survival analysis with treatment condition (MBCT/m-ADM) as the independent variable and allowing for the stratification variables. In a secondary analysis ADM use will be added as an independent variable in the Cox regression model. A per protocol analysis will also be undertaken for the secondary outcomes.

Secondary outcomes will be examined using mixed models Analysis of Variance (ANOVA): between group (ITT/per protocol) and repeated measures (3-24 month follow-ups). Sensitivity analyses will explore the impact of imputation of data losses including loss to follow up and drop out.

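### The baseline score is not a fixed term in the secondary-outcome model: it enters only an adjusted version, and only if the arms happen to differ on it

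*Protocol article*

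**What the plan says.** Three parts of the protocol article bear on this.

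- **(i) The policy question** gives one method for the secondary outcomes as a class: "Secondary outcomes will be examined using mixed models Analysis of Variance (ANOVA): between group (ITT/per protocol) and repeated measures (3-24 month follow-ups". Arm and visit are the only terms named. The stratification variables are named for the primary Cox model in the preceding paragraph, but not here.
- **Statistical analysis plan**, opening paragraph, sets a rule for every model. Each is to be run "with and without adjustment for baseline characteristics where the covariate selection is derived from comparison of the treatment groups at baseline". The article does not say which of the two versions carries the conclusion.
- **Setting, participants, recruitment and randomization** shows that depressive symptoms are measured at entry. Randomisation is stratified by locality and by "participants' symptomatic status at intake assessment", using a GRID-HAMD cut-off of 8.

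The outcomes concerned are of different kinds. HRSD, BDI-II and EQ-5D are scores. The Secondary outcomes section adds "Psychiatric co-morbidity will be assessed with the full SCID" and "Depression free days will be calculated from the SCID", and antidepressant use is also listed as secondary. On power, the Sample size section says that the planned sample "will enable us to detect a medium between-groups effect size (standardised mean difference or Cohen's d = 0.40) on the main secondary outcomes".

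**The concern.** A baseline covariate is worth including because it predicts the outcome. Whether the randomised arms happen to differ on it is a separate matter, and in a randomised trial any such difference is due to chance. A rule that admits covariates by comparing the arms will leave out a strongly prognostic baseline score whenever the arms are balanced on it.

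For the Hamilton score the stratification makes this more likely. Balancing the arms on symptomatic status at intake reduces the observed difference, and so the chance that the rule selects the score.

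Two things are at stake. One is precision on residual symptoms and quality of life, which could be gained without extra patients. The other is that the covariate set depends on the observed data and no version is designated as the main one, so two results can stand side by side with no stated order between them.

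A smaller matter is that one ANOVA is named for outcomes that may not all be scores on a continuous scale.

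**Working it through.** **Inputs from the article (Sample size, Table 1).** 210 per group, from "This leads to a total sample size of 420 across the two groups"; attrition 20%; design factor 1.11 (ICC 0.01, group size 12: 1 + 11 × 0.01); significance 0.05, taken as two-sided. The text gives 80% power and the note under Table 1 gives 90%, so both are shown.

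**Assumption.** The correlation ρ between baseline and follow-up scores is not in the article. A range of 0.3 to 0.7 is used. Patients enter in full or partial remission, which narrows the spread of baseline scores, so the low end cannot be ruled out.

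**Step 1: the article's own figure.** Effective patients per arm = 210 × 0.8 / 1.11 = 151.4. With the SD set to 1, the standard error of a difference in means is √(2/151.4) = 0.115.

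- Power for d = 0.40 without baseline: Φ(0.40/0.115 − 1.96) = Φ(1.52) ≈ 94%.
- Patients needed for d = 0.40: 99 per arm at 80% power, or 99 × 1.11 / 0.8 = 138 after inflation; 132 at 90%, or 132 × 1.11 / 0.8 = 184. Both are below 210.

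The d = 0.40 statement is therefore confirmed and is conservative.

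**Step 2: effect of always including the baseline score, one visit.** Adjustment multiplies the variance by 1 − ρ². The detectable d is 2.8016 × 0.115 × √(1 − ρ²) at 80% power and 3.2415 × 0.115 × √(1 − ρ²) at 90%, with 0.11495 used unrounded.

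| ρ | 1 − ρ² | Variance cut | Equivalent sample, 1/(1 − ρ²) | Detectable d, 80% | Detectable d, 90% | Power for d = 0.30 |
|---|---|---|---|---|---|---|
| unadjusted | 1.00 | – | 1.00 | 0.322 | 0.373 | 74% |
| 0.3 | 0.91 | 9% | 1.10 | 0.307 | 0.355 | 78% |
| 0.4 | 0.84 | 16% | 1.19 | 0.295 | 0.342 | 81% |
| 0.5 | 0.75 | 25% | 1.33 | 0.279 | 0.323 | 85% |
| 0.6 | 0.64 | 36% | 1.56 | 0.258 | 0.298 | 90% |
| 0.7 | 0.51 | 49% | 1.96 | 0.230 | 0.266 | 95% |

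**Step 3: averaging over visits.** Take four follow-ups (an assumption) and the same correlation ρ between all occasions. The variance of the mean is (1 + 3ρ)/4 unadjusted, and adjustment subtracts ρ².

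- ρ = 0.3: 0.475 to 0.385, ratio 0.81
- ρ = 0.5: 0.625 to 0.375, ratio 0.60
- ρ = 0.7: 0.775 to 0.285, ratio 0.37

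The relative gain is larger than at one visit. If baseline correlates less with the follow-ups than these do with each other, it will be smaller than shown.

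**Step 4: outcomes that may not suit the ANOVA.** The article gives no rates or distributions for co-morbidity, antidepressant use or depression-free days, so no figure can be computed for them.

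**The case against.** The strongest reply is that the article does plan adjustment. The rule in the Statistical analysis plan section covers all models, and the 3–24 month wording names the levels of the repeated factor without excluding covariates. This stands in part. A reader might infer that secondary outcomes are analysed with no baseline adjustment at all, and the document does not support that. It does state the rule by which covariates enter, and that rule does not guarantee the baseline score. This is a stated choice, so it is not a detail left to a fuller plan.

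A second reply is that no stated aim fails. That is correct: a reader might infer that the trial is underpowered for its secondary outcomes, but Step 1 shows otherwise. The cost is wider intervals and less power for effects below 0.40.

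A third reply concerns outcome type. A reader might take co-morbidity to be binary and depression-free days to be one skewed total per patient, and conclude that the ANOVA gives poor standard errors and uninterpretable means. The article does not give the scoring. Its use of Cohen's d for secondary outcomes, with psychiatric co-morbidity among those expected to show medium effects, fits a count or score at least as well. Depression-free days could also be computed per follow-up interval. With about 168 completers per arm, a comparison of means is fairly robust to skew. This part therefore holds only conditionally.

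Finally, mixed models ANOVA may already mean a likelihood-based mixed model. Nothing here depends on its being otherwise.

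**Conclusion.** The point holds in a limited form. The secondary-outcome model names arm and visit only. The baseline score can enter just the adjusted version, and only through chance imbalance between the arms, and no version is declared the main one. For an assumed correlation of 0.3 to 0.7, fixing the baseline score in the model would cut single-visit variance by 9% to 49%. At 0.5 the cut is 25%, and the detectable d moves from 0.32 to 0.28 at 80% power, or from 0.37 to 0.32 at 90%. These sizes rest on the assumed correlation and on the article's own attrition and design factor.

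This is a gain forgone on secondary outcomes. It does not threaten the d = 0.40 statement. The mismatch between the ANOVA and some outcome types is a secondary point that depends on scoring the article does not give.

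**What to change.** - For each continuous score with a baseline measurement (HRSD, and BDI-II and EQ-5D where they are collected at baseline), always include the baseline value and the stratification factors (locality, symptomatic status) in the repeated-measures model, and name that model as the main one.
- Drop covariate selection by comparing the arms at baseline. An unadjusted version can remain as a sensitivity analysis.
- State how co-morbidity and depression-free days are scored. If co-morbidity is diagnosis present/absent, use a logistic mixed model or GEE. If depression-free days are a single 24-month total, compare them once with bootstrap or robust intervals. The article already uses a bootstrap check for skewed costs, in item (d) under (ii) The explanatory questions.

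The cost is a change of wording, made before unblinded outcome data are seen. No new assessment is needed for the Hamilton score, which is taken at intake. For BDI-II and EQ-5D the article does not say whether a baseline value is collected, and this should be confirmed.

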#### (ii) The explanatory questions

These will be examined using a mix of three mutually informative methods:

(a) For the MBCT arm time to relapse/recurrence of depression will be compared using Cox regression proportional hazard survival analysis, allowing for the stratification variables and any group differences in ADM tapering/usage (if rates of tapering/usage are different across the two arms).

(b) Mediational analyses will investigate hypothesised mechanisms of change pre-/post-treatment across the trial arms using approaches to testing mediation that allow multiple mediators in one model using the approach set out by Kraemer et al. (2002) and as used in our exploratory trial [49].

(c) Qualitative data will be analysed using thematic analysis (with NVivo software). This will combine inductive and deductive approaches and will be conducted collaboratively by a small sub-group of the research team in order to enhance validity.

The Data Monitoring and Safety Committee will oversee analysis at 3 and 12 months for patient safety and at 12 and 24 months for the primary outcome analyses. Given the public health importance of the findings we anticipate disseminating the findings at 12 and 24 month follow-ups as soon as they are available.

(d) Differences in mean costs will be analysed using standard parametric t-tests with the validity of results confirmed using bias-corrected, nonparametric bootstrapping (repeat re-sampling) [50]. Despite the skewed nature of cost data, this approach is recommended to enable inferences to be made about the arithmetic mean [51]. The primary economic analysis will focus on the policy question: MBCT vs. mADM. Cost-effectiveness will be assessed through the calculation of incremental cost-effectiveness ratios (ICER) and will be explored in terms of relapse/recurrence and quality adjusted life years using the EQ-5D measure of health-related quality of life. Uncertainty around the cost and effectiveness estimates will be represented by cost-effectiveness acceptability curves [52].

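### The randomisation strata are named for the Cox models but not for the secondary-outcome ANOVA, and the stated covariate rule would not bring them in; continuous secondary outcomes would be tested somewhat conservatively

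*Protocol article*

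**What the plan says.** All references are to the protocol article.

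- **Setting, participants, recruitment and randomization.** The allocation "will use permuted block randomisation using computer generated quasi-random numbers". Further, "Randomisation will be stratified according to recruitment locality (4 sites, enabling a steady flow to treatment groups) and participants' symptomatic status at intake assessment", with a GRID-HAMD score of 8 as the cut. Four localities by two symptom levels make eight strata.
- **(i) The policy question, primary outcome.** The Cox model is fitted "with treatment condition (MBCT/m-ADM) as the independent variable and allowing for the stratification variables".
- **(ii) The explanatory questions, item (a).** The Cox model there is again described as "allowing for the stratification variables and any group differences in ADM tapering/usage".
- **(i) The policy question, secondary outcomes.** "Secondary outcomes will be examined using mixed models Analysis of Variance (ANOVA): between group (ITT/per protocol) and repeated measures (3-24 month follow-ups"). No stratification factor is named.
- **Statistical analysis plan, opening paragraph.** Every model is to be run both unadjusted and adjusted for baseline characteristics, and for the adjusted version the "covariate selection is derived from comparison of the treatment groups at baseline".

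**The concern.** Permuted blocks within strata make the arms nearly identical on locality and on intake symptom status. Variation between strata therefore drops out of the true sampling error of the arm difference. A linear model without the strata leaves that variation in its residual, so it reports a standard error larger than the true one.

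The adjusted version of each analysis does not repair this. A rule that looks for differences between the arms at baseline will pass over the factors that the design has made equal. Read literally, neither version of the secondary analysis would then contain the strata.

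The effect should be largest for residual depressive symptoms. One stratum is a cut of the Hamilton score at intake, the HRSD is a follow-up outcome, and the BDI-II measures the same construct. At stake is the width of the intervals, and some power, on outcomes that the trial presents as important to patients and policy makers.

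**Working it through.** **Inputs from the article (Sample size section and Table 1).** 210 per group; attrition 20%; ICC 0.01; group size 12; significance 0.05 (taken as two-sided); stated detectable effect on the main secondary outcomes d = 0.40.

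**Assumptions.** The article does not give R², the share of variance in the patient's outcome (averaged over visits) that the strata explain. I use 2%, 10% and 20%. A smaller effect, d = 0.32, is added because it is roughly what this sample detects with 80% power.

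**1. The plan's own claim on secondary outcomes.** The design factor is 1 + 11 × 0.01 = 1.11, as in Table 1. The effective number per group is 210 × 0.80 / 1.11 = 151.4. In units of the outcome's SD, the standard error of a mean difference is √(2/151.4) = 0.115. At d = 0.40 the standardised effect is 0.40 / 0.115 = 3.48, and power is Φ(3.48 − 1.96) = 93.6%. The claim that d = 0.40 is detectable is confirmed.

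**2. Would the covariate rule select the strata?** A simulation used eight strata, blocks of 4 (the article gives no block size), 336 patients and 4,000 runs per scenario. A comparison of the arms at p < 0.05 selected symptom status or locality in 0 of 4,000 runs in every scenario.

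**3. Reported against true standard error.** The true standard error is √(1 − R²) times the one reported without strata. So:

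- reported / true standard error = 1/√(1 − R²)
- true type I error = 2 × [1 − Φ(1.96/√(1 − R²))]

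| R² | Reported / true SE | True type I error |
|---|---|---|
| 2% | 1.010 | 4.8% |
| 10% | 1.054 | 3.9% |
| 20% | 1.118 | 2.8% |

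**4. Power.** With the strata in the model, power = Φ(δ − 1.96), where δ = d / (0.115 × √(1 − R²)). Without them δ is unchanged, because the design has already removed the between-stratum variance, but the critical value becomes 1.96/√(1 − R²). For example, at d = 0.40 and R² = 10%, δ = 3.67 and the critical values are 1.96 and 2.07, giving 95.6% and 94.5%.

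| R² | d = 0.40, without → with | d = 0.32, without → with |
|---|---|---|
| 2% | 93.8 → 94.0% | 79.7 → 80.3% |
| 10% | 94.5 → 95.6% | 80.7 → 83.5% |
| 20% | 95.5 → 97.3% | 82.2 → 87.5% |

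**5. Sample-size equivalent.** I solved for the number of patients at which the test without strata matches the power of the test with them. At d = 0.32 this is about 1%, 7% and 15% more patients for R² of 2%, 10% and 20%. At d = 0.40 it is about 1%, 6% and 12%.

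**6. Check by simulation (same set-up as step 2).** Without strata the mean reported standard error was 0.109 throughout. The actual SD of the estimate was 0.103 to 0.106 at R² = 10% and 0.098 to 0.101 at R² = 18%. With strata the reported values were 0.103 and 0.099, close to the truth. Power at d = 0.30 rose from 79.5% to 82.1% (R² 10%) and from 80.5% to 85.7% (R² 18%). At R² = 2% it moved only from 78.3% to 79.0%.

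**The case against.** The best defence is that this rests partly on silence in a condensed article. One sentence names the method, the between-patient factor and the repeated factor. A full list of model terms is usually left to the analysis plan, and nothing in the article expressly rules the strata out. Moreover, the baseline-comparison rule applies to all models, and the Cox models carry the strata all the same. The authors therefore can enter strata independently of that rule and may intend to do so here. This part stands: a reader might infer that the plan excludes the strata from the secondary analyses, and the text does not go that far.

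The defence does not remove the point. The article takes the trouble to name the strata for two Cox models and omits them from the secondary model, and the only covariate rule it gives cannot supply them. Anyone working from this text would arrive at a model without them.

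The defence is also right about size. At the planned effect there is little power left to gain. A reader might take 1/(1 − R²), that is 11% to 25% at R² of 10% to 20%, as the equivalent in extra patients. That figure describes only the width of the reported interval. Stratified randomisation has already made the estimate itself more precise, so the equivalent in power is the smaller one in step 5. Finally, R² of 10% to 20% is argued mainly for symptom scores. Outcomes weakly related to site and intake severity would sit near the 2% row, where the effect is negligible.

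**Conclusion.** The point holds as a modest one. Followed as written, the continuous secondary outcomes would be analysed with standard errors about 1%, 5% or 12% too large for an assumed R² of 2%, 10% or 20%. At the stated d = 0.40 the cost is about 0.2, 1 or 2 points of power. Only if true effects are smaller does it reach about 3 to 5 points, and then only with strata that explain 10% to 20% of the variance.

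Three stronger conclusions should not be drawn:

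- **Invalid results.** The estimates are unbiased and the error is conservative, so false positives are not inflated.
- **All secondary outcomes.** The standard-error argument is for continuous outcomes in a linear model. For a binary outcome such as psychiatric co-morbidity under a logistic model, leaving out the strata would instead attenuate the odds ratio.
- **The primary analysis or the sample size.** Neither is touched; the primary Cox model already has the strata.

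The result depends on R², which the article does not give, and on an analysis plan, not shown here, leaving the secondary model as the article describes it.

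**What to change.** State that locality and intake symptom stratum enter the secondary-outcome models as prespecified fixed effects, as in the primary Cox model, and that they stay in whatever the baseline comparison shows. The covariate rule in the opening paragraph of the statistical analysis plan section should exempt them explicitly.

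The cost is one clause and four degrees of freedom (three for locality, one for symptom status). Both factors are already recorded at randomisation, so no new data are needed.
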